## Abstract

**Introduction:**

Chronic low back pain is a common condition that imposes an enormous burden on individuals and society. Physical exercise with education is the most effective treatment, but generally results in small, albeit significant improvements. However, which type of exercise is most effective remains unknown. Core stability training is often used to improve muscle strength and spinal stability in these patients. The majority of the core stability exercises mentioned in intervention studies involve no spinal movements (static motor control exercises). It is questionable if these exercises would improve controlled movements of the spine. Sensor-based exergames controlled with spinal movements could help improve movement control of the spine. The primary aim of this study is to compare the effects of such sensor-based exergames to static motor control exercises on spinal movement control.

**Methods and analysis:**

In this quasi-randomized controlled trial, 60 patients with chronic low back pain who are already enrolled in a multidisciplinary rehabilitation programme will be recruited. Patients will be randomly allocated into one of two groups: the Sensor-Based Movement Control group (*n* = 30) or the Static Motor Control group (*n* = 30). Both groups will receive 8 weeks of two supervised therapy sessions and four home exercises per week in addition to the rehabilitation programme. At baseline (week 1) and after the intervention (week 10), movement control of the spine will be assessed using a tracking task and clinical movement control test battery. Questionnaires on pain, disability, fear avoidance and quality of life will be taken at baseline, after intervention and at 6- and 12 months follow-up. Repeated measures ANOVAs will be used to evaluate if a significant Group x Time interaction effect exists for the movement control evaluations.

**Discussion:**

Sensor-based spinal controlled exergames are a novel way to train spinal movement control using meaningful and engaging feedback. The results of this study will inform clinicians and researchers on the efficacy of movement control training for patients with low back pain.

**Ethics and dissemination:**

Ethical approval for this study protocol was obtained from the METC Brabant (protocol number NL76811.028.21).

**Trial registration:**

Open Science Framework Registries (https://osf.io/v3mw9/), registration number: 10.17605/OSF.IO/V3MW9, registered on 1 September 2021.

## Introduction

Low back pain is extremely common. More than 50% of the population will experience one or more episodes of low back pain during their lifetime (1). Most episodes of low back pain resolve within 6 weeks, but in some cases the symptoms return regularly. In those cases where symptoms persist for more than 3 months, there is a chronic condition with a variable course (2, 3). According to current evidence, the best treatment for low back pain is exercise, preferably in combination with education, but thus far, to the best of our knowledge there is no evidence that certain exercises work better than others (4).

In a considerable part of the intervention studies with a focus on physical exercises, “core stability” interventions are offered (5). During these interventions, patients are taught to selectively contract the deep trunk muscles (m. Transversus Abdominis and mm. Multifidi) in various postures and during various movements of the extremities. The lumbar spine is fixated in neutral lordosis in most of these exercises (6). We will refer to this type of exercise as “static motor control exercise” henceforth. Although these exercises have been shown to be effective in pain reduction, they are not superior to other physical exercise interventions (6).

Some patients with low back pain fixate their spine (i.e., they demonstrate reduced range of motion) during every-day movements (7–11). This behavior could be stimulated further with static motor control exercises. Moreover, several low back pain patients do experience problems with spinal movement control (12), i.e., adapting the direction, speed, and amplitude of spinal movement to the demands of the task at hand.

Designing exercises to improve movement control of the spine is a challenge. In a recent paper by Hooker et al., patients with low back pain received patient specific training to modify their altered movement pattern during functional activities (13). This resulted in a more normal distribution of hip, knee and spinal movements when picking up an object at shank height. Although this study shows that training can improve the relative contribution of joint movements during functional tasks in low back pain patients, it is no direct evidence that spinal movement control has improved.

Movement control over less centrally located joints, such as the elbow or knee, can be trained using functional tasks, like bringing a spoon to the mouth or kicking a ball toward a pylon. The success of the execution (not spilling the soup or knocking over the pylon) can be used as an indication of good control over the movement of the joint. Providing meaningful feedback on spinal movements is more complicated. Sensors that measure spinal movements can offer a solution (14). There are several sensor-based training systems available on the market, but currently only a few randomized controlled trials incorporating these technologies have been published (15, 16). These sensor-based training systems can be used to offer accurate real-time feedback on spinal movements, which could help to improve spinal movement control. These systems provide the possibility to train spinal movement control relatively independent without the need of intensive supervision and/or a highly experienced therapist (17). Moreover, the training sessions are relatively easy to standardize and the progression from simple toward complex movements can easily be adapted to each patient's abilities and needs. The sensor-based exergames could be more engaging and motivating than conventional motor controlexercises, which might increase therapy adherence (18).

This paper describes the protocol for a randomized controlled trial to evaluate if a sensor-based movement control intervention enhances movement control of the spine in low back pain patients to a greater extent than a standard static motor control intervention. We will assess movement control using a custom made spinal movement controlled tracking task and a clinical test battery by Luomajoki et al. (19, 20). We hypothesize that a sensor-based movement control intervention will enhance movement control of the spine in low back pain patients measured by spinal movement controlled tracking tasks to a greater extent than a standard static motor control intervention. The majority of the tests in the clinical test battery by Luomajoki et al. (19, 20) involve no spinal movement, hence we hypothesize that the static motor control group will improve more on this outcome than the sensor-based movement control group.

To confer clinical benefit beside movement control of the spine, we will also evaluate differences between the offered interventions in terms of therapy adherence, their respective effects on disability, pain intensity, fear avoidance beliefs, and health related quality of life.

## Methods

### Design

In this single-center quasi-randomized controlled trial, 60 low back pain patients will be quasi-randomly assigned to either the Sensor-Based Movement Control group (*n* = 30) or the Static Motor Control group (*n* = 30) (Figure 1). Both interventions are nested within a 12-week multidisciplinary rehabilitation programme for low back pain at the Military Rehabilitation Centre “Aardenburg” (MRC), Doorn, The Netherlands. This study protocol was approved by the METC Brabant (protocol number NL76811.028.21). Informed consent will be obtained from all patients prior to entry into the study by one of the investigators ([name]). This trial received funding of the Stichting Ziektekostenverzekering Krijgsmacht (SZVK) in the Netherlands. This study design follows the recommendations of SPIRIT 2013 (Supplementary material 1).

**Figure 1 F1:**
[figure not shown]
Flowchart for participants of this study. *-T2 two weeks for T0; -T1 one week for T0; T0 week 1; T1 week 10; T2 week 26; T3 week 52.

### Study setting

Patients will be recruited from both the inpatient and outpatient population of the MRC. Approximately 100 low back pain patients are treated in the Centre each year (21). With an inclusion rate of 80% and a dropout rate of 20%, inclusion can be completed in ~1 year and the final follow-up can be completed ~2 years after the start of the study. Enrolment started on 17 May 2021 and is ongoing. Data collection is in progress.

### Patient and public involvement

There has been no patient and public involvement as co-producers of this study.

### Randomization, blinding and treatment allocation

This study is quasi-randomized and non-concealed. Patients will be screened in the first week of the multidisciplinary rehabilitation programme (2 weeks prior to baseline data collection). Enrolment and allocation will be 1 week prior to baseline data collection after consent of the patient. Patients will be enrolled and allocated to each intervention by one of the investigators ([name]) based on the starting date of the multidisciplinary rehabilitation programme. The research team has no influence on the starting date of each patient. If two patients start on the same date, allocation order will be alphabetically (based on the patients last name). The first five patients were allocated to the static motor control group, followed by five patients in the sensor-based movement control group and so forth until 30 patients have completed each intervention. This random allocation sequence was chosen by the investigators to keep group therapy planning feasible. Patients and therapists will not be blinded as this is practically impossible, however they will not be informed about the hypotheses of the study. The primary study outcome (spinal movement tracking error) will be calculated using a computer algorithm (custom made in D-flow, Motek, Amsterdam, The Netherlands) that will work independent of treatment allocation. Investigators involved in the statistical analysis will not be blinded to group. The clinical movement control battery tests will be recorded on video and scored by two examiners that are blinded to time (before/after intervention) and allocation.

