### Interventions

The Sensor-Based Movement Control and Static Motor Control intervention will be offered over a course of 8 weeks (weeks 2–9 of the study), each week consisting of two supervised therapy sessions of 20–30 min and four non-supervised home exercises of 5–10 min resulting in nearly one training session every day of the week for 8 weeks.

The supervised sessions are provided by five experienced (4–10 years) physio- and occupational therapists from the MRC that are trained to provide both the intended interventions. The therapists can also provide the regular therapies in the multidisciplinary rehabilitation programme of a patient. Three training moments are given to all therapists at the same time by the investigators to understand the content of the interventions and how to offer this to the patients during 8 weeks. The quality will be assured by several evaluation meetings with the investigators and investigators will check the content of the sessions by occasionally being present at the supervised sessions throughout the study. The first four sessions will be individual, i.e., one patient supervised by one therapist. In these sessions, the capacity of the patient will be determined by the therapists and the patient will get acquainted with the basics of the training. The final 12 sessions will be in groups, with a maximum of three patients in the same intervention per session, supervised by one therapist. The patients will not have the same therapist throughout the programme to keep the rehabilitation planning feasible. The therapists will monitor the progress and challenge the patient if needed during all sessions. There is a standard protocol for exercises throughout the sessions, for both the sensor-based movement control and static motor control group. This protocol was composed by two experienced physiotherapists/human movement scientists and are based on literature (6). Therapists are allowed to modify the standard exercises to match the difficulty level to the capacity of the patient. The standard exercises can also be deviated from to the need of the individual patient as long as it is within the scope of the assigned intervention. There is no standardized approach for modifications in progression, however all modifications will be registered. An example of the protocol for week four is presented in Figure 2. Attendance of the supervised sessions will be registered.

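### Allocation in known runs of five, unconcealed and made a week before T0, leaves routes for selection and baseline bias that T0 before disclosure would narrow; correlation within runs is a secondary, conditional risk

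*Protocol article*

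**What the plan says.** The section Randomization, blinding and treatment allocation is open about the method: "This study is quasi-randomized and non-concealed". Order of entry follows the programme start date, with ties broken by last name. On the sequence: "The first five patients were allocated to the static motor control group, followed by five patients in the sensor-based movement control group", continuing until 30 patients have completed each intervention. On who does it: "Patients will be enrolled and allocated to each intervention by one of the investigators". On timing: "Enrolment and allocation will be 1 week prior to baseline data collection after consent of the patient". Patients and therapists are not blinded, but are not told the hypotheses.

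The safeguard offered against selection is "The research team has no influence on the starting date of each patient". Under Participants, screening is done by a physician and a manual therapist. Tracking error is computed by an algorithm, and the clinical test battery is scored from video by raters blinded to time and allocation.

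Under Interventions, training runs in weeks 2 to 9, and "The final 12 sessions will be in groups, with a maximum of three patients in the same intervention per session". Under Statistical analysis, the ANOVA has Group, Time and Group x Time only. There is no term for run or therapy group and no adjustment for baseline differences.

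The wording is not consistent. The same section that declares quasi-randomisation also says "This random allocation sequence was chosen by the investigators", and the Abstract says "Patients will be randomly allocated into one of two groups". The limitations in the Discussion do not mention the allocation method.

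**The concern.** Three separate things could go wrong.

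- **Selection.** Screening and consent take place after the programme start date has fixed the order, when the next arm is already foreseeable. Some exclusion criteria need judgement, and each exclusion or refusal shifts who falls into which run.
- **Baseline.** T0 includes an effort-dependent tracking task and self-report questionnaires, and it follows allocation by a week. If the patient knows the arm by then, effort or answers could differ by arm before any training. The analysis measures change from T0, so such a difference would look like a treatment effect, or mask one.
- **Precision.** Patients in a run share a calendar period and an arm, and most of their supervised sessions are in small same-arm groups. If their changes are correlated, treating patients as independent gives a standard error that is too small.

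**Working it through.** **The plan's own figure.** The Sample size section gives N = 54 (27 per group) at 95% power for an effect size of 0.25. With 2 groups, 2 times, Cohen's f = 0.25, alpha 0.05 and an assumed correlation of 0.5 between T0 and T1 (not stated), lambda = f² x N x 2 / (1 - 0.5) = 0.25N. At N = 54 the noncentral F test has power 0.9501, so the figure reproduces. It treats patients as independent.

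**Predictability.** 60 patients in runs of 5 make about 12 runs, 6 per arm (approximate, because drop-outs are replaced). The order is fixed and unconcealed, so the next arm is always known, against about a 50% chance of a correct guess under concealed simple 1:1 randomisation.

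**How a T0 shift enters.** The interaction estimate is (T1 - T0) in the sensor arm minus (T1 - T0) in the static arm. If knowing the arm shifts mean T0 by s in one arm relative to the other, and T1 is unaffected, the estimate moves by s in full. Algorithmic or blinded scoring does not change this: it protects the score given to a performance, not the performance itself, and it does not touch the questionnaires. The documents give no basis for the size or direction of s.

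**Correlation within runs.** For two time points, the Group x Time test is a t-test on change scores. With cluster size m and intraclass correlation ICC of the *change score*:

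- design effect DE = 1 + (m - 1) x ICC
- actual type I error of the nominal 5% test ≈ 2 x (1 - Φ(1.96/√DE))

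The documents give no ICC, so the values are assumed. Cluster size 5 is the allocation run; 3 is the largest therapy group.

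| ICC | DE, m = 5 | Type I, m = 5 | DE, m = 3 | Type I, m = 3 |
|---|---|---|---|---|
| 0 | 1.00 | 5.0% | 1.00 | 5.0% |
| 0.01 | 1.04 | 5.5% | 1.02 | 5.2% |
| 0.05 | 1.20 | 7.4% | 1.10 | 6.2% |
| 0.10 | 1.40 | 9.8% | 1.20 | 7.4% |

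A simulation of 12 alternating runs of five (100,000 trials) agrees for m = 5: 5.0%, 5.5%, 7.4% and 9.9%. Required N for m = 5 is 54 x DE: 56.2, 64.8 and 75.6 at ICC 0.01, 0.05 and 0.10. The last two exceed the planned 60.

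**Which model term helps.** Write the outcome of patient i in run j at time t as fixed effects + u(j) + b(i) + e(ijt). The change from T0 to T1 contains no u(j), because it cancels. A random intercept for run therefore leaves the interaction test as it was. The term has to act on the change: a random run effect on T1 - T0, or equivalently run-by-time.

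**Cost of a run-level test.** Under the plan's assumptions (f = 0.25, correlation 0.5), equating 0.25N with N x d²/4 gives a change-score effect of d = 1. A t-test on 12 run means (10 df) at N = 60 has power 0.936, 0.889 and 0.838 at ICC 0, 0.05 and 0.10. The patient-level test has 0.968 if patients are independent.

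**The case against.** The defence has real substance.

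- **The design is declared and reasoned.** The article calls itself quasi-randomised and non-concealed, and the runs exist so that group therapy can be planned. A reader might infer from the words random and randomly that the trial is passed off as randomised. The documents do not support that; the wording is loose beside plain declarations in the Abstract and in Design.
- **Selection is partly guarded.** Clinicians screen, start dates lie outside the team's control, and allocation follows consent. This lowers the risk. It does not remove it, because nothing says that those who screen or obtain consent are unaware of the sequence.
- **T0 is partly guarded.** Hypotheses are withheld, and the article does not say when patients learn their arm. If that already happens after T0, the patient-side risk is absent. But nothing in the article says the arm is withheld until then.
- **Correlation may be small.** A run is an allocation unit, not a treatment unit. The first four sessions are individual, home exercises are unsupervised, patients do not keep one therapist, and all therapists are trained to deliver both interventions. Because the arms alternate, slow calendar drift largely balances. Run effects that are constant over time cancel from the interaction.

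The last point stands to a large degree. A reader might infer that the planned p-values are certainly too small. That needs a positive ICC of the change score, which the documents do not give.

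**Conclusion.** The allocation facts are all in the article: fixed known runs of five, no concealment, one investigator enrolling and allocating, allocation a week before T0, and unblinded patients. They leave open a route for selection and a route for an arm-related shift at T0, which would pass undiluted into the unadjusted Group x Time effect. Neither bias is demonstrated, and neither can be sized from the documents. A reader might go further and take the baseline as compromised; nothing in the article shows that.

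The standard-error issue is secondary and conditional. For assumed ICCs of 0.01 to 0.10, type I error would be about 5.5% to 9.8% with clusters of five, or 5.2% to 7.4% with clusters of three, and there is no inflation at ICC 0.

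This should be addressed, because the main remedy is cheap and enrolment was ongoing when the article was written.

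**What to change.** 1. **Order of steps, for remaining patients.** Record eligibility and consent, and complete T0, before the arm is disclosed to the patient and, where existing staffing allows, to the T0 tester. T0 is in week 1 and training starts in week 2, so the runs of five and the group planning can stay.
2. **Sensitivity analysis.** Add a random run effect on the T1 - T0 change score (equivalently a run-by-time term) with small-sample degrees of freedom, or a t-test on run means. A run random intercept alone is not enough.
3. **Wording.** Change "This random allocation sequence was chosen by the investigators" and "Patients will be randomly allocated into one of two groups" to say quasi-random, and list the allocation method among the limitations.

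Redrawing the order of runs within static/sensor pairs is not worth doing unless the draw is concealed from the enrolling investigator. The first patient of each pair would reveal the other nine, so 6 x 9 = 54 of 60 assignments would stay predictable.

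**Cost.** Step 1 is a mid-trial procedural change: earlier and later patients would have T0 under different conditions, and under Dissemination a significant modification must be communicated to the ethics committee, funder, registry and sponsor. Planners will still know the arm early, so foreknowledge at enrolment is reduced only as far as eligibility is recorded first. Step 2 needs no new patients, but its intervals will be somewhat wider. Step 3 is text only.

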### Data management

Patients will receive a unique three-digit number that will be used on all forms (except the informed consent form) used in this study. Only the principal investigators will have access to the key of this code list. The informed consent and patient related forms will be stored separately from the other forms and will be stored for 15 years. Video-recordings of the clinical movement control test battery will be stored locally at the MRC. Only the principal investigators will have access to these recordings. The recordings will be scored by two independent physical therapists, under supervision of a principal investigator.

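### The analysts are to know each patient's group, no reason is given, and the choice of leading movement control outcome is not settled; arms should stay coded until the planned tests are final

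*Protocol article*

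**What the plan says.** On analysis, the section Randomization, blinding and treatment allocation states: "Investigators involved in the statistical analysis will not be blinded to group". Of the other parties it says: "Patients and therapists will not be blinded as this is practically impossible". On allocation it says: "This study is quasi-randomized and non-concealed". Assignment follows the programme start date in runs of five: "The first five patients were allocated to the static motor control group, followed by five patients in the sensor-based movement control group", and so on.

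The same section describes two protections at outcome assessment. The tracking error comes from a computer algorithm "that will work independent of treatment allocation". The clinical test battery is filmed and "scored by two examiners that are blinded to time (before/after intervention) and allocation".

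Data management adds two statements. On the list linking study numbers to patients: "Only the principal investigators will have access to the key of this code list". On the videos: "The recordings will be scored by two independent physical therapists, under supervision of a principal investigator". It also restricts access to the recordings to the principal investigators.

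**The concern.** Patients and therapists know the group and allocation can be foreseen, so the later steps at which group knowledge can be kept out carry more weight. Analysis is one of them, and the plan opens it by rule. If the people processing and analysing the data see the labels, any remaining choice can be made, even unintentionally, with knowledge of which arm it favours. Such choices include how signals are handled, who is excluded and which movement control result leads the report. The Group x Time contrast could then be biased in an unknown direction.

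A related, smaller question is the scoring of the clinical battery. It is masked, but it is supervised by a role that may know the allocation.

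**Working it through.** No figure in the plan depends on this point, so the check sets the relevant sections of the article side by side.

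1. **Is there a reason for the unblinded analysis?** For patients and therapists the plan cites practical impossibility. For analysts it cites nothing. Nothing in the described design prevents a recoded group column.

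2. **Is there a direction to favour?** Yes. The Introduction expects the sensor-based group to improve more on the tracking tasks and the static group to improve more on the clinical battery. With labels visible, each result can be read at once as supporting or opposing a stated hypothesis.

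3. **What is fixed?** Statistical analysis fixes the repeated measures ANOVA, alpha 0.05, parametric tests whatever the distribution, no baseline adjustment, exclusion below 10 sessions, complete-case handling and the software.

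4. **What is still open?** Mainly which result leads.
   - Randomization, blinding and treatment allocation calls the tracking error the primary study outcome.
   - Primary outcome names movement control, measured by three tracking tasks and the clinical battery.
   - Discussion says the main outcome will be analysed with three assessments. One is the self-developed test, which is listed under Secondary outcomes.
   - Statistical analysis plans five Group x Time tests: three tracking tasks, their average, and the battery total (3 + 1 + 1 = 5). It gives no order among them.
   - The missing-data sentence on the t-tests does not make clear which complete-case set applies to which comparison.

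5. **Would coding the arms A/B be enough?** Not alone. Allocation alternates in runs of five by start date, and the article states that the static group came first. Start dates, or study numbers if they run in enrolment order (the article does not say), would reveal the arm. Therapists' notes on exercise modifications could reveal it too. Numbers must therefore be scrambled, and dates and notes kept out of the file.

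6. **Is the video scoring compromised?** The two raters are described as blinded under both Randomization and Primary outcome, and as independent under Data management. The code list is described as linking number to patient, not as an allocation list. A supervising principal investigator could still know a patient's group, because allocation is open and follows start date and investigators sometimes attend sessions (Interventions). The article does not say what supervision covers. The self-developed test is rated in the same way, so the same question applies to it.

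**The case against.** The strongest case on the other side is that the plan discloses the unblinded analysis, fixes most of it in advance, derives the tracking error by algorithm and keeps the video raters blinded. Patients and therapists are also not told the hypotheses. All of this stands, and it keeps the point small. It does not settle which outcome leads, and it does not explain why analysts need the labels.

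Four stronger readings are tempting, and the article does not support them.

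- **The masking of video scoring is lost.** A reader might infer this from the supervision sentence together with the code key. No section says that the supervisor rates, cues the raters, tells them the time point or consults the key. Some involvement also follows from the access rule, since only principal investigators may reach the recordings. Barring every key holder from scoring would conflict with that rule.
- **The trial has no blinding, or only two safeguards remain.** The blinded raters and the allocation-independent algorithm are both in the plan.
- **Five tests at 0.05 give the size of the problem.** A family-wise error rate across five tests measures multiplicity. Coding the arms leaves all five tests at the same alpha, so such a figure would be the same before and after the fix. The tests are not independent either, because one is the average of three others.
- **The remedy is free.** It is cheap, but someone has to prepare the coded file.

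Discussion also mentions subgroup exploration. That remark concerns power for pain and disability and does not open the main contrast. Detailed scoring logistics may properly sit in the full protocol. The sentence on analysts is different, because it is a stated rule and not an omitted detail.

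**Conclusion.** The point holds as a minor design weakness: group labels are open at analysis by rule and without a reason, in a trial with open allocation, stated directional hypotheses and an unsettled primary outcome. It is a cheap improvement, not a correction of an error. Any bias is of unknown size and direction. The route is indirect for the algorithm-derived tracking error, and for the clinical battery at the scoring stage it exists only if supervision were to leak the group. The supervision sentence needs a clarification and nothing more.

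The conclusion assumes that the analysts share, or at least know, the hypotheses in the article, and that no coding rule elsewhere overrides the quoted sentence. Study setting reports enrolment and data collection as in progress, so on the article's own account the change could still be made.

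**What to change.** **In Randomization, blinding and treatment allocation,** replace the sentence on analysts with a rule to this effect: the analysis is run on a file in which groups are coded A and B, patient numbers are scrambled, and dates and session notes are absent; the code is broken only after signal processing, the 10-session exclusion and the planned tests are final.

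The cost is modest. A person who does not run the analysis must prepare the file and hold the code. The session-count exclusion must be applied before the file is made, or outside it, because attendance records and notes could unmask the arms. No additional assessment or patient contact is needed.

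**In Data management,** add one sentence limiting the principal investigator's supervision of scoring to access, file handling and training before the first rating, with no comment on individual ratings. This keeps the existing restriction on access to the recordings.

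Reconciling the three descriptions of the primary outcome and ranking the five tests is a separate task. Coding the arms does not replace it.
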